### Sample Size Calculation

The sample size was calculated using G*Power version 3.1 based on an independent 2-group comparison (2-tailed independent-sample *t* test). Because previous studies investigating breast milk odor in preterm infants reported heterogeneous interventions, outcome measures, and effect estimates that were not directly comparable with the present study, a medium standardized effect size (Cohen *d*=0.50) was selected in accordance with Cohen’s recommendations for clinical research [20]. Assuming a 2-sided significance level of .05 and a statistical power of 80%, the minimum required sample size was 86 infants. To account for an anticipated 10% attrition rate, the final target sample size was increased to 96 infants, with 48 participants allocated to each group.

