### Outcome Measures

The primary outcome of this study was feeding cues, as measured by the FCF-UF. Feeding cues were assessed 3 times daily during each feeding session over the 3-day intervention period (total of 9 assessments). The assessments were conducted using video recordings, which were evaluated by a blinded pediatric nursing specialist to ensure objectivity and reduce observer bias.

The secondary outcome was the time to first successful breastfeeding, defined as the duration (in minutes) from the onset of observable feeding cue behaviors until the infant achieved the first successful breastfeeding. Observable feeding cue behaviors included rooting, head turning toward the breast, mouth opening, and searching for the nipple following tactile stimulation. Successful breastfeeding is defined as effective latching onto the mother’s breast followed by coordinated sucking, swallowing, and breathing for a sustained period, as observed by trained clinical staff.

Although breastfeeding attempts may occur during routine clinical care during the 3-day intervention period, these routine attempts were not included in the assessment of the secondary outcome. To ensure a standardized observation period across all participants, the predefined secondary outcome (time to first successful breastfeeding) was prospectively measured beginning on day 4, after completion of the intervention. Observations were conducted daily for a maximum of 60 minutes per day and continued for up to 10 days or until successful breastfeeding was achieved.

This outcome was measured using a stopwatch starting from day 4 after completion of the intervention. The measurement of time to first successful breastfeeding therefore began after completion of the 3-day intervention period (day 4). Postnatal age and other relevant clinical variables were recorded and will be considered as potential confounders in the analysis.

All outcome data were recorded in structured electronic forms immediately after each assessment to ensure accuracy and completeness. The schedule of enrollment, intervention, and outcome assessments is presented in Table 1.

**Table 1. T1:** Schedule of enrollment, intervention, and outcome assessments.

Study phases	Day 0	Days 1‐3	Days 4‐10
Screening and eligibility	✓		
Informed consent	✓		
Randomization	✓		
Intervention (breast milk odor exposure)		✓^a^	
Feeding cue assessment (FCF-UF^b^)		✓^c^	
Time to first successful breastfeeding			✓^d^

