### Data Analysis

Data analysis will be conducted according to the intention-to-treat principle; therefore, all randomized participants will be included in the analysis according to their assigned groups, regardless of their adherence to the intervention. Outcomes will be analyzed using an independent *t* test for normally distributed data or the Mann-Whitney *U* test when normality assumptions are not met. If repeated measurements are available across multiple points, longitudinal analysis will be performed to more comprehensively assess response changes over time. For the secondary outcome of time to first successful breastfeeding, Kaplan-Meier survival analysis will be used, with between-group comparisons performed using the log-rank test. Infants who do not achieve successful breastfeeding within the 10-day observation period will be treated as censored observations. Intervention effects will be reported as the mean difference between groups, accompanied by effect sizes, using Cohen *d* to describe the magnitude of the intervention’s impact.

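### Mean difference with Cohen d is the only effect measure named, and it is not well defined for the censored breastfeeding-time outcome

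*Protocol article*

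**What the plan says.** All of the analysis wording is in one paragraph of the protocol article, Methods, Data Analysis.

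- Outcomes in general get a t test, or "the Mann-Whitney *U* test when normality assumptions are not met".
- The secondary time outcome has its own method: "Kaplan-Meier survival analysis will be used, with between-group comparisons performed using the log-rank test".
- The censoring rule comes next in the paragraph: "Infants who do not achieve successful breastfeeding within the 10-day observation period will be treated as censored observations".
- The closing sentence follows directly: "Intervention effects will be reported as the mean difference between groups, accompanied by effect sizes, using Cohen *d* to describe the magnitude".

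No hazard ratio, median time, restricted mean or rank-based estimate is named anywhere in the article. The paragraph also promises an intention-to-treat analysis that keeps every randomized infant.

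The Outcome Measures section bears on the time scale. The secondary outcome is "defined as the duration (in minutes) from the onset of observable feeding cue behaviors" up to the first success, taken by stopwatch, while "Observations were conducted daily for a maximum of 60 minutes per day and continued for up to 10 days".

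**The concern.** The plan names the log-rank test for breastfeeding time. That test yields a P value but no effect size. The one effect measure the plan then names presupposes that each infant has an observed time and that each arm has an ordinary mean and standard deviation. A censored infant has only a lower bound on the time.

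This goes beyond detail that an article may leave to an analysis plan: a measure is stated, and it does not fit the censoring rule two sentences before it. Earlier breastfeeding is part of both the objective and the hypothesis, so its effect size is likely to be quoted. If it is computed carelessly, the reported size and the log-rank P value would describe different quantities.

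A smaller version of the problem affects the feeding cue score. If the normality check sends the analysis to the Mann-Whitney test, the P value concerns the ordering of the two distributions, while the estimate beside it would be a difference in means.

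**Working it through.** **Inputs from the protocol.** Log-rank comparison, censoring at the end of a 10-day window, intention to treat, and mean difference with Cohen d as effect measure (Data Analysis). Outcome in minutes and at most 60 minutes of observation a day (Outcome Measures). 10% attrition anticipated (Sample Size Calculation). The protocol gives no success rate, hazard ratio or share censored, so it has no figure on this point to reproduce.

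**Inputs assumed.** Exponential times counted in days from the start of observation, L = 10 days, hazard ratio (HR) 1.5 or 2.0, and control-arm censored share c from 5% to 50%. The day scale is itself an assumption, because the outcome is defined in minutes.

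**Formulas.** λ0 = −ln(c)/L and λ1 = HR·λ0.

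- Censored infants set to L: RM(λ) = (1 − e^(−λL))/λ. If all censoring falls at L, this is exactly the restricted mean.
- Censored infants dropped: EV(λ) = (RM(λ) − L·e^(−λL))/(1 − e^(−λL)).

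**One case in full (HR 1.5, c = 20%).** λ0 = 0.1609 and λ1 = 0.2414; the intervention-arm share censored is 0.2^1.5 = 8.9%.

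- Restricted means are 3.77 and 4.97 days, a difference of −1.20.
- After dropping, the means are 3.16 and 3.71, a difference of −0.55.
- Share kept: 0.55/1.20 = 46%.

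**Range (differences in days; shares from unrounded values).**

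| Control censored | HR 1.5: restricted / dropped | Kept | HR 2.0: restricted / dropped | Kept |
|---|---|---|---|---|
| 5% | −0.97 / −0.70 | 72% | −1.51 / −1.17 | 78% |
| 10% | −1.10 / −0.66 | 60% | −1.76 / −1.16 | 66% |
| 20% | −1.20 / −0.55 | 46% | −1.99 / −1.02 | 51% |
| 30% | −1.19 / −0.45 | 38% | −2.03 / −0.86 | 42% |
| 50% | −1.00 / −0.28 | 28% | −1.80 / −0.55 | 30% |

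At 0.01% control-arm censoring, dropped, restricted and unrestricted differences agree to two decimals (−0.36 at HR 1.5, −0.54 at HR 2.0).

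**Cohen d.** At HR 1.5 the uncensored value is −0.39. With 20% of controls censored it is −0.36 if they are set to the limit and about −0.22 if they are dropped. At HR 2.0 the corresponding values are −0.63, −0.64 and −0.41. So d changes little at low censoring when times are set to the limit, but it then standardizes by a standard deviation that depends on the length of the window.

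**Second check, day-by-day success.** Assume daily success of 10% against 20% over 10 days. Then 0.9^10 = 35% and 0.8^10 = 11% are censored.

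- Restricted means, (1 − (1−p)^10)/p, are 6.51 and 4.46, a difference of −2.05.
- Among successes only, the means are 4.65 and 3.80, a difference of −0.85, or 41% of −2.05.

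**The two routes against the plan.** Dropping infants makes inclusion depend on success after randomization, so the arms compared are no longer those randomized. Setting times to the limit works only if every censored infant was followed to the limit. An infant lost earlier, which the attrition allowance makes possible, has no known status there.

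**Mann-Whitney.** No arithmetic is needed. The difference in sample means stays unbiased for the difference in means whichever test is run. What fails is the pairing of that estimate with a P value for a different quantity.

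**The case against.** The strongest reply is that the closing sentence was written for the feeding cue score. Mean difference and Cohen d suit that score, and the sample size rests on the same scale: "a medium standardized effect size (Cohen *d*=0.50) was selected" for a t test. That may well be the intention, and the sentence does not say that it covers every outcome. But it follows straight after the survival sentences and excepts nothing. If it was meant only for the cue score, breastfeeding time has no named effect measure, and the text still needs a line.

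A reader might infer that the breastfeeding effect will be biased, perhaps badly. The document does not support that.

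- Dropping unsuccessful infants would breach the plan's own intention-to-treat and censoring sentences, so the successes-only figures show what to avoid and not what is planned.
- The only censoring described is at a common end of follow-up. There, setting times to the limit gives the restricted mean difference, a valid estimate if so named.
- Comparing it with an unrestricted mean would extrapolate beyond the window, to a quantity the plan does not target.

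Two further replies stand. The planned Kaplan-Meier analysis already yields success proportions and, where reached, medians, so the plan is not limited to a P value. And the event rates above are assumptions, in days, for an outcome defined in minutes. They show direction and range, and do not predict this trial's result.

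**Conclusion.** The point holds as a mismatch in the stated effect measure. The plan names one measure without exception, and that measure is not well defined for a censored outcome compared by log-rank.

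Any distortion depends on the share censored and on how those infants are handled. It is negligible with few censored infants. In the assumed scenarios, dropping them shrinks the effect towards zero, by 22% to 28% at 5% control-arm censoring and 49% to 54% at 20%. Setting them to the limit costs nothing against the restricted mean if all censoring is administrative.

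The minutes-against-days question in the outcome definition must be settled first, because a restricted mean or a hazard ratio has meaning only on a stated scale. The Mann-Whitney part is a mismatch between test and estimate and should not be read as bias.

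**What to change.** 1. Limit the mean difference and Cohen d to the feeding cue score.
2. For time to first successful breastfeeding, state one time origin, unit and window length. Report a hazard ratio and/or a restricted mean time difference over that window, with 95% CI, beside the Kaplan-Meier success proportions. Either measure is acceptable; the hazard ratio adds a proportional-hazards assumption, and the restricted mean does not.
3. Say how infants lost before the end of the window are handled, and do not compute a mean among successes only.
4. If the Mann-Whitney test is used for the feeding cue score, report an estimate that goes with it, such as the Hodges-Lehmann shift or the probability of superiority, or give the mean difference with its own CI.

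No new data are needed and the output is standard. The article reports statistical analysis as completed in August 2026, so the cost is a little re-reporting, to be disclosed as a change to the planned effect measures.

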### Data Monitoring

Due to the minimal risks involved, a data monitoring committee was not established. The research team monitored all events throughout the study.

### Strategies for Improving Adherence

To ensure protocol adherence, the researchers implemented several monitoring strategies during the intervention. The intervention schedule—administered 3 times daily—was consistently maintained through coordination with the NICU nursing team, who provided reminders and helped ensure that each intervention was delivered according to the established timeline. In addition, feeding cues were assessed using the FCF-UF by trained observers, specifically pediatric nursing specialists with at least 5 years of NICU clinical experience, ensuring the quality and consistency of assessment throughout the study.

### Dissemination Plan

Study findings will be submitted to peer-reviewed journals and presented at scientific meetings. Results will also be shared with participating hospitals to inform local neonatal nursing practice.

## Results

This study was funded in May 2025. Recruitment commenced in December 2025 and was completed in March 2026, with a total of 104 participants enrolled. Baseline demographic and clinical characteristics, including gestational age, birth weight, and clinical stability, were collected for all participants. Data collection was completed in April 2026, followed by data cleaning and statistical analysis, which were completed in August 2026. No major deviations from the study protocol have been identified. The study findings are expected to be disseminated in 2026.

## Discussion

### Principal Findings

This study is designed to evaluate whether breast milk odor improves feeding cues and shortens the time to first successful breastfeeding in preterm infants. If beneficial, the intervention may represent a simple sensory-based strategy that can be integrated into routine NICU care.

### Comparison With Prior Work

Previous studies have consistently suggested that breast milk odor may improve feeding readiness and facilitate the transition to oral feeding in preterm infants. Recent systematic reviews and meta-analyses also reported beneficial effects on feeding outcomes, physiological stability, and selected clinical outcomes among preterm infants. However, these reviews also highlighted substantial heterogeneity in intervention protocols, outcome measures, participant characteristics, and methodological quality. Many included studies were conducted in single centers with relatively small sample sizes, limiting the strength and generalizability of the available evidence [4,6].

Among individual randomized trials, Yücel et al [9] demonstrated improvements in feeding cues and earlier transition to oral feeding following breast milk odor exposure, while Mohamed Soliman et al [13] reported enhanced feeding progression and behavioral responses. Despite these promising findings, differences in intervention delivery, assessment methods, and study design make direct comparisons difficult. These limitations underscore the need for standardized randomized controlled trials using validated outcome measures.

The present study was designed to address these gaps by using a multicenter randomized controlled design with concealed allocation, blinded outcome assessment, and a standardized breast milk odor protocol administered 3 times daily for 3 consecutive days. Unlike previous studies, feeding cues are assessed repeatedly using the validated FCF-UF, allowing comprehensive evaluation of behavioral changes over time. Conducting this study in 2 tertiary NICUs in Indonesia also provides context-specific evidence from a Southeast Asian setting where standardized developmental care interventions remain limited. Collectively, these methodological improvements are expected to strengthen the current evidence and support the integration of breast milk odor as a simple, low-cost intervention to promote feeding readiness in preterm infants.

### Strengths and Limitations

Strengths of this study include the randomized controlled design, standardized intervention procedures, and use of validated outcome measures. Blinded outcome assessment may also reduce measurement bias. Several limitations should also be considered. First, complete blinding is not feasible because of the nature of the intervention. Second, natural variation in breast milk composition between mothers may influence odor characteristics. Third, the study is conducted in selected NICUs, which may limit generalizability to other settings.

### Future Directions

Future research should examine longer-term outcomes, including feeding independence, growth, breastfeeding continuation, and neurodevelopment. Multicenter trials with larger and more diverse populations would further strengthen external validity.
